#### Analysis of vital sign variables

Not applicable

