# Flow Chart

## Study flow chart

| **STUDY PARAMETERS** | **REFERENCE DAYS FOR ALL ATTACKS** | | | | | | | | |  |
| --- | --- | --- | --- | --- | --- | --- | --- | --- | --- | --- |
| D0  V1  Inclusion visit | *D1**  *V2* | *D2**  *V3* | D3  V4  End of trt visit | D7  1d  V5 | D14  1d  V6 | D21  1d  V7 | D28  2d  V8 | D42 2d  V9  End of follow up visit | Un  sche  duled visit |
| Medical history | x |  |  |  |  |  |  |  |  |  |
| Age/Weight/Size/sex | x |  |  |  |  |  |  |  |  |  |
| Physical examination / Vital Signs | x | x | x | x | x | x | x | x | x | x |
| Clinical Tolerability: clinical signs | x | x | x | x | x | x | x | x | x | x |
| Parasitemia  thick and thin smear | x | x | x | x | x | x | x | x | x | x |
| Haemoglobin | x |  |  | x | x | x |  | x | x† | (x) |
| Platelets+ leukocytes + neutrophils | x |  |  |  | x | x |  | x | x† | (x) |
| Creatinemia | x |  |  |  | x | x |  | x | x† | (x) |
| ALT, total bilirubin | x |  |  |  | x | x |  | x | x† | (x) |
| Filter paper for PCR if thick smear + | x |  |  |  | (x) | (x) | (x) | (x) | (x) | (x) |
| Filter paper for DSAQ or L dosage | x# |  |  | x | x |  |  |  |  |  |
| AE record |  | x | x | x | x | x | x | x | x | x |
| Study treatment | x | x | x |  |  |  |  |  |  |  |
| Concomitant treatments | x | x | x | x | x | x | x | x | x | x |

* visits carried out at the 1st attack only

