## Exclusion criteria

### Specific exclusion criteria for initial enrollment

- Plan to permanently move out of the investigator site area in the duration of the trial
- patient participating in another ongoing clinical trial
- allergy to one of the investigational medicinal products
- history of hepatic and (or) haematological impairment during treatment with amodiaquine
- history of cardiac disease
- concomitant febrile illness

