### Exclusion criteria for each attack

- presence of at least one danger sign of malaria: recent history of convulsions (1-2 within 24h),unconsciousness state, lethargy, unable to drink or breast feed, vomiting everything, unable to stand/sit due to weakness
- severe concomitant disease or known disturbances of electrolyte balance such as hypokalaemia or hypomagnesaemia
- intake of medication metabolised by cytochrome CYP 2D6 (e.g. metoprolol, flecainide, imipramine, amitriptyline, clomipramine) at the time of inclusion
- intake of drugs known to inhibit CYP 2A6 (e.g. methoxsalem, pilocarpine, tranylcypromine) and/or 2C8 cytochromes (e.g. trimethoprim, ritonavir, ketoconazole, montelukast, gemfibrozil) at the time of inclusion
- intake of medication known to prolong the QTc interval, such as class IA and III antiarrythmics, neuroleptics, antidepressant agents, certain antibiotics including drugs in the macrolide class, fluoroquinolones, imidazole and triazole, antifungal agents, certain non-sedative antihistamines (terfenadine, astemizole) and cisapride at the time of inclusion
- patient having received artesunate + amodiaquine or artemether + lumefantrine at

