### Methods of assessment

- Physical and Clinical signs and symptoms: the following signs and symptoms will be examined systematically by the investigator and described as being absent, mild, moderate, severe or life threatening: weakness, muscle and/or joint aches, headache, anorexia, nausea, vomiting, abdominal pain, diarrhea, cough, pruritus, tinnitus, behavioural changes, flu, convulsion, dehydration, jaundice, chest ,abdomen, skin (cf. Appendix 2 for grading all of them), Hackett splenic score (score from 0 to 5: Appendix 2d)
- Temperature: axillary temperature will be taken using an electronic thermometer
- Blood pressure (SBP, DBP in mmHg), respiratory rate (pm) and pulse rate (bpm) will be measured after resting for 10 minutes in the sitting position.
- Microscopy

Blood samples will be collected from patients for thick and thin blood smears on days 0, 1, 2, 3, 7, 14, 21, 28, 42 and on any unscheduled day that the patient presents with clinical deterioration or recurrent fever. About a drop of blood is collected for each smear. Thick and thin blood smears obtained from fingerpick blood samples will be stained with Giemsa and read by experienced laboratory technologists who are not directly involved in direct patient care. Parasite and gametocyte densities will be calculated from thick blood smears and thin smears will be used for parasite species identification (Appendix 6). Urgent thick smears will be read in our study clinic for initial diagnosis and to identify treatment failures during follow-up. Routine blood smears will be read within 48 hours. For quality control, all slides will be read by a second microscopist and a third reviewer will settle any discrepant readings.

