## Visit schedule

### Inclusion visit: D0

The following tests will be carried out:

- Physical examination, collection of medical history, concomitant treatments and demographic data (age, sex), together with body weight and height,
- Vital signs: blood pressure, respiratory and pulse rates at rest, axillary temperature
- Clinical signs and symptoms
- Haematological and biochemical analyses
- Thick and thin smear and filter paper blood spot samples
- Treatment administration
- For 2nd and following attacks:
- Delivery of treatments and patient booklet
- Filter paper blood spot sample for potential DSAQ / L dosage

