#### Vital signs

- Axillary temperature at each time of measurement

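### Section 14.5.4.3 rules out any vital-sign analysis, although section 11.1 makes vital signs part of the safety evaluation and section 14.3.3.3 lists one as a safety variable

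*Protocol*

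**What the plan says.** **Collection.** Section 10.1.3 states: "Blood pressure (SBP, DBP in mmHg), respiratory rate (pm) and pulse rate (bpm) will be measured after resting for 10 minutes". The D0 list in section 13.2.1 asks for "Vital signs: blood pressure, respiratory and pulse rates at rest, axillary temperature". The study flow chart (section 2.1) has a row headed "Physical examination / Vital Signs" that is ticked at all nine scheduled visits and at unscheduled visits. The visit lists for D1 to D3 (13.2.2), for D3 of repeat attacks (13.2.3) and for D7 to D42 (13.2.4) ask for a physical examination and axillary temperature, and do not name blood pressure, pulse or respiratory rate.

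**Role in safety.** Section 11.1 says that safety and tolerability rest on recorded adverse events and on graded laboratory and vital-sign evaluations. Section 14.3.3.3 lists one vital-sign safety variable: "Axillary temperature at each time of measurement".

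**Analysis.** The whole content of section 14.5.4.3 is "Not applicable". Section 14.1 makes Section 14 the foundation of the statistical analysis plan.

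**Adverse-event route.** Section 11.7 admits a vital-sign abnormality as an adverse event only when it is medically relevant: symptomatic, needing corrective treatment, leading to discontinuation, serious, or an event of special interest.

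**The concern.** A protocol can reasonably leave the layout of safety tables to the statistical analysis plan. Here it does not leave the matter open: it states that no vital-sign analysis applies, in the section on which that plan is to be built. A statistician following it would produce no vital-sign table, while section 11.1 tells the reader that graded vital signs contribute to the safety conclusion.

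At stake is a by-arm description of blood pressure, pulse and respiratory rate during and after treatment, across repeated attacks over two years. The protocol sets the effect of repeated treatment on tolerability as an objective (section 6.2). A shift in one arm too small to bring any child over the section 11.7 threshold would be measured, stored and never shown.

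**Working it through.** No figure in the plan is in dispute. The check sets the sections side by side.

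1. **Is 14.5.4.3 compatible with 11.1?** No. Section 11.1 pairs laboratory and vital-sign grading as the second strand of the safety evaluation. Laboratory variables then receive, in 14.5.4.2, summaries by arm at each time point, counts by grade, a between-arm comparison and change from baseline. Vital signs receive nothing.

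2. **Is it compatible with 14.3.3.3?** Not as worded. Temperature is listed there as a safety variable at every measurement. Section 14.5.3.2 analyses it as efficacy: absence of fever from D1 to D3 in the first attack and at D3 in repeat attacks. Later readings feed the response classification, but no summary of the values is planned.

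3. **Can the promised grading be done?** Only in part. Appendix 2b grades temperature (headed as tympanic, whereas section 10.1.3 takes it in the axilla) and grades respiratory rate within the chest row. Pulse and blood pressure have no row of their own; pulse appears only among the signs of dehydration, and low pressure only within the vomiting and diarrhoea rows.

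4. **Does adverse-event reporting fill the gap?** For clinically important changes, yes. Section 11.7 brings them in, 14.5.4.1 tabulates treatment-emergent events by system organ class, intensity and seriousness, and 10.2.3 compares adverse-event indices between arms. Below the threshold, no: the special-interest events in 11.8 concern only neutrophils, ALT and bilirubin, so that clause adds no vital sign.

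5. **How much data is affected?** There are four variables without any planned safety output: systolic pressure, diastolic pressure, pulse and respiratory rate. The number of visits after D0 depends on which section governs:
   - Flow chart: D0, D1, D2, D3, D7, D14, D21, D28 and D42 are 9 scheduled visits. That gives 9 − 1 = 8 after D0 in the first attack. D1 and D2 belong to the first attack only, so repeat attacks have 8 − 2 = 6.
   - Visit lists 13.2.2 to 13.2.4: none of the four is named after D0, so 0 visits.

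   Under the first reading, on-treatment values exist and are not used. Under the second, only D0 values exist and no change can be described. The protocol does not say which applies, and section 10.1.3 gives no schedule for these measurements.

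6. **Why age matters.** Children enter at 6 to 59 months and are followed for up to two years, so a child may reach 59 + 24 = 83 months. Resting pulse, respiratory rate and blood pressure change with age over that span, so pooled raw values across attacks would mix age with treatment.

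**The case against.** The strongest reply is that little is lost. Cardiac adverse events, serious events and deaths are collected and tabulated, and medically relevant vital-sign abnormalities join them. The one vital-sign variable that 14.3.3.3 lists, temperature, is analysed by arm under efficacy, so the entry in 14.5.4.3 might simply mean that nothing further was intended. The other signs may not be measured after D0 at all: the flow-chart row combines examination and vital signs, and temperature plus an examination could satisfy it. Most of this stands, and it keeps the point small. It does not remove the conflict with section 11.1, and the benign reading of 14.5.4.3 is not what the text says.

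Two stronger readings are tempting, and the protocol does not support them.

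- A reader might infer that pulse, blood pressure and respiratory rate are the only cardiovascular safety data in the trial, so that cardiovascular safety goes unexamined. Sections 11.7, 14.5.4.1 and 10.2.3 show otherwise; what goes unsummarised is measured values below the adverse-event threshold.
- A reader might note the exclusions for "history of cardiac disease" and "intake of medication known to prolong the QTc interval", see that no ECG is scheduled, and conclude that a vital-sign analysis would cover QT risk. Resting pulse and blood pressure do not measure the QT interval, so it would not. Nor does the protocol state an expected effect of either drug on pulse or blood pressure.

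**Conclusion.** The contradiction is real and explicit: 14.5.4.3 conflicts with 11.1 and, as worded, with 14.3.3.3, while 10.1.3, 13.2.1 and the flow chart show that the data are collected. As written, four measured vital-sign variables have no safety output by arm except through adverse events.

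This is a minor point. It does not touch the primary endpoint or the non-inferiority conclusion, and nothing in the protocol shows that either treatment shifts these signs. How much usable data is at issue rests on an unresolved question, namely whether blood pressure, pulse and respiratory rate are taken after D0. Between 0 and 8 later scheduled visits are involved in a first attack, and between 0 and 6 in a repeat attack. The statistical analysis plan is not at hand; if it does contain vital-sign tables, it departs from the section on which it is meant to rest, and the protocol wording still needs correcting.

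**What to change.** 1. Reconcile the flow chart with sections 13.2.1 to 13.2.4, so that the protocol states at which visits blood pressure, pulse and respiratory rate are measured, in first and in repeat attacks.
2. List every vital sign actually collected in 14.3.3.3.
3. Replace the entry in 14.5.4.3 with a descriptive summary by arm and by attack at each visit where the signs are measured. Add change from D0 where later values exist, and allow for age, for instance by presenting the summaries within age bands. For temperature, cross-refer to the fever analyses in 14.5.3.2. Formal adjusted comparisons are not needed to repair this point.
4. Make section 11.1 match: either say how pulse and blood pressure are graded, or limit the grading statement to the signs that have a scale.

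If the sponsor prefers no vital-sign analysis, the protocol should say why and amend 11.1 and 14.3.3.3 to agree.

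The cost is a few extra safety tables and small wording edits to the protocol. If the flow chart already reflects what is done, no new measurement is required.

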## Interim analysis

No interim analysis is planned for this study.

# Ethical and regulatory standards

## Ethical principles

This Clinical Trial will be conducted in accordance with the principles laid down by the 18th World Medical Assembly (Helsinki, 1964) and all applicable amendments laid down by the World Medical Assemblies and the ICH guidelines for Good Clinical Practice (appendix 8).

## Laws and regulations

This Clinical Trial will be conducted in compliance with all international laws and regulations, and national laws and regulations of Uganda, as well as any applicable guidelines.

## Informed consent

The Investigator (according to applicable regulatory requirements), or a person designated by the Investigator, should fully inform the patient and the parent[s] or guardian[s] of all pertinent aspects of the clinical trial including the written information given approval / favorable opinion by the Faculty of Medicine Makerere University Research and Ethics Committee (FOMREC), Uganda National Council of Science and Technology UNCST, the Uganda National Drug Authority, NDA. All participants should be informed to the fullest extent possible about the study in language and terms they are able to understand.

Prior to a patient’s participation in the clinical trial, the Informed Consent Form should be signed and personally dated by the patient’s parent(s) or by the patient’s legally acceptable representative, and by the person who conducted the informed consent discussion. Whenever possible, the consent will be signed by both parents/guardians. If only one parent or guardian signs the consent form, the investigator must document the reason for only one parent or guardian’s signature. If they are unable to sign, they may place their fingerprint or a cross on the consent form.

For patients unable to read or understand English or the local dialect, the patient information leaflet and consent form will be read out and explained in the parent/guardian’s local dialect in the presence of a witness who will also sign the consent form to confirm that the parent/guardian has freely given his/her consent.

Only one informed consent will be signed at the patient’s inclusion into the cohort, the duration of the study (including passive follow-up) will be explained to parent/guardian. Prior to include a patient in a new episode follow-up, an oral consent has to be obtained from parent/guardian.

The person discussing this information with the patient will also sign and date the consent form.

## Institutional Review Board/Independent Ethics Committee (IRB/IEC)

The Investigator or the Sponsor must submit this Clinical Trial Protocol to the appropriate Ethics Committee (the Faculty of Medicine Makerere University Research and Ethics Committee (FOMREC), Uganda National Council of Science and Technology (UNCST), the Uganda National Drug Authority, (NDA)), and is required to forward to the Sponsor a copy of the written and dated approval/favorable opinion signed by the Chairman with Ethics Committee (FOMREC, UNCST and NDA). In compliance with international recommendations, a similar protocol performed in Senegal (including children and adults and with a 28 day follow-up) has been submitted for consultation to a French IEC.

The Clinical Trial (study number, Clinical Trial Protocol title and version number), the documents reviewed (Clinical Trial Protocol, Informed Consent Form, Summary of Product Characteristics, Investigator’s CV, etc.), the list of voting members and their qualifications and the date of the review should be clearly stated on the written (FOMREC) approval/favorable opinion.

Investigational Product will not be released at the study site and the Clinical Trial will not start until a copy of this written and dated approval/favorable opinion has been received by the Sponsor.

During the Clinical Trial, any amendment or modification to the Clinical Trial Protocol should be submitted to the Faculty of Medicine Makerere University Research and Ethics Committee (FOMREC), Uganda National Council of Science and Technology (UNCST), the Uganda National Drug Authority, (NDA). It should also be informed of any event likely to affect the safety of patients or the continued conduct of the Clinical Trial, in particular any change in safety. All updates to the Investigator’s Brochure will be sent to the Faculty of Medicine Makerere University Research and Ethics Committee (FOMREC), Uganda National Council of Science and Technology (UNCST), the Uganda National Drug Authority, (NDA?.

A progress report shall be sent to the Faculty of Medicine Makerere University Research and Ethics Committee (FOMREC), Uganda National Council of Science and Technology (UNCST), the Uganda National Drug Authority, annually or as prescribed and a summary of the Clinical Trial’s outcome at the end of the Clinical Trial. Any serious adverse reactions and/or unanticipated effects on subjects which may occur as a result of this study shall be immediately reported to the FOMREC, UNCST and NDA. The FOMREC Continuing annual Review Form shall be completed and submitted annually to the review board (when due) as well as the Final/Study termination form at the end of the proposed study . The final study report shall be submitted to the FOM-REC using a standard form.

# Study monitoring

## Responsibilities of the Investigator(s)

The Investigator(s) undertake(s) to perform the Clinical Trial in accordance with this Clinical Trial Protocol, ICH guidelines for Good Clinical Practice and the applicable regulatory requirements.

The Investigator is required to ensure compliance with all procedures required by the Clinical Trial Protocol and with all study procedures provided by the Sponsor (including security rules). The Investigator agrees to provide reliable data and all information requested by the Clinical Trial Protocol (with the help of the Case Report Form [CRF], Discrepancy Resolution Form [DRF] or other appropriate instrument) in an accurate and legible manner according to the instructions provided and to ensure direct access to source documents by Sponsor representatives.

The Investigator may appoint such other individuals as he may deem appropriate as Sub-Investigators to assist in the conduct of the Clinical Trial in accordance with the Clinical Trial Protocol. All Sub-Investigators shall be appointed and listed in a timely manner. The Sub-Investigators will be supervised by and under the responsibility of the Investigator. The Investigator will provide them with a copy of the Clinical Trial Protocol and all necessary information.

## Responsibilities of the Sponsor

The Sponsor of this Clinical Trial is responsible to Health Authorities for taking all reasonable steps to ensure the proper conduct of the Clinical Trial Protocol as regards ethics, Clinical Trial Protocol compliance, and integrity and validity of the data recorded on the Case Report Forms. Thus, the main duty of the Monitoring Team is to help the Investigator and the Sponsor maintain a high level of ethical, scientific, technical and regulatory quality in all aspects of the Clinical Trial.

At regular intervals during the Clinical Trial, the site will be contacted, through monitoring visits, letters, emails or telephone calls, by a representative of the Monitoring Team to review study progress, Investigator and patient compliance with Clinical Trial Protocol requirements and any emergent problems. During these monitoring visits, the following but not exhaustive list of points will be scrutinized with the Investigator: patient informed consent, patient eligibility, patient recruitment and follow-up, Serious Adverse Event documentation and reporting, Investigational Product allocation, patient compliance with the Clinical Trial Protocol and the Investigational Product regimen, Investigational Product accountability, concomitant therapy use and quality of data.

## Source document requirements

According to the ICH guidelines for Good Clinical Practice, the Monitoring Team must check the Case Report Form entries against the source documents, except for the pre-identified source data directly recorded in the Case Report Form. The Informed Consent Form will include a statement by which the patient allows the Sponsor’s duly authorized personnel, the Faculty of Medicine Makerere University Research and Ethics Committee (FOMREC), Uganda National Council of Science and Technology (UNCST), the Uganda National Drug Authority, (NDA) to have direct access to source data which support the data on the Case Report Forms (eg, patient's medical file, appointment books, original laboratory records, etc.). Such personnel, bound by professional secrecy, must keep confidential all personal identity or personal medical information (according to confidentiality rules).

## Use and completion of Case Report Forms (CRFs) and additional request

It is the responsibility of the Investigator to maintain adequate and accurate CRFs (according to the technology used) designed by the Sponsor to record (according to Sponsor instructions) all observations and other data pertinent to the clinical investigation. All CRFs should be completed in their entirety in a neat, legible manner to ensure accurate interpretation of data.

Should a correction be made, the information to be modified must not be overwritten. The corrected information will be transcribed by the authorized person next to the previous value, initialed and dated.

The collection of the CRF will be done by the monitor after the whole completion of the CRF.

The computerized handling of the data by the Sponsor after receipt of the CRFs may generate additional requests (DRF) to which the Investigator is obliged to respond by confirming or modifying the data questioned. The requests with their responses will be appended to the CRFs held by the Investigator and the Sponsor.

